### Sample size estimation

This is a pilot trial to assess the changes in bone microstructure affected by luseogliflozin treatment compared with metformin treatment, evaluated by HR-pQCT. There is no prior similar study comparing the bone strength before and after the intervention that can be used to estimate the precise optimal sample size. Julious et al. reported that 12 participants per group are needed for a pilot study [22]. The justification for this sample size is based on the rationale concerning feasibility and precision regarding the mean and variance of the primary outcome measures.

### Patients and public involvement statement

There is no patient or public involvement in this trial.

### Participants and recruitment

A total of 24 participants aged ≥ 60 years will be recruited into the study. The enrollment started in June 2019. All participants have been diagnosed with T2DM, and their cases have never been complicated with osteoporosis. Patients fulfilling the inclusion criteria described below will be invited to a screening for their eligibility. The principal investigator and co-investigators recruit the participants among their outpatients, and obtain a written informed consent from the participants. There are no additional consent provisions for the collection and use of participant data and biological specimens in ancillary studies. The recruitment rate and the consent rate will be evaluated at the end of the study.

### Inclusion criteria

As shown in Fig. 1, participants must fulfill the following criteria to be eligible for inclusion at their first visit to Nagasaki University Hospital (visit 1): (1) an individual aged ≥ 60 years; (2) diagnosed with T2DM; (3) an outpatient; (4) treated with diet therapy alone or with orally administered antidiabetic agents including metformin (≤ 1000 mg/day), and/or an alpha-glucosidase inhibitor (α-GI) and/or a dipeptidyl peptidase-4 (DPP-4) inhibitor, whose treatment has not been changed within 6 months before enrollment; and (5) providing written informed consent.

### Run-in criteria

Participants will be included when they also fulfill the following criteria at week 0 (visit 2): (1) the patient’s HbA1c (National Glycohemoglobin Standardization Program: NGSP) level is ≥ 7.0% and < 9.0%; (2) the patient’s T score in both lumbar vertebrae and the femoral neck determined by DXA is > − 2.5 standard deviations (SDs).

### Exclusion criteria

Eligible participants will be excluded if they meet any of the following criteria: (1) have a previous history of treatment with a SGLT2 inhibitor; (2) are complicated by a bone metabolic disorder (i.e., osteomalacia, thyroid dysfunction, hyperparathyroidism, or hypoparathyroidism which requires any medical treatments); (3) have been administered any treatment for osteoporosis within 12 months before enrollment (e.g., a bisphosphonate, vitamin D preparation, vitamin K preparation, calcium preparation, selective estrogen-receptor modulator, antireceptor activator of nuclear-factor kappa-Β ligand antibody (denosumab), anti-sclerostin antibody (romosozumab), or recombinant human PTH (teriparatide)); (4) are being treated with estrogen or testosterone hormone replacement therapy; (5) are complicated by diabetic retinopathy and/or diabetic neuropathy that required therapeutic intervention; (6) have severe renal dysfunction defined as an estimated glomerular filtration rate (eGFR) < 30 mL/min/1.73 m^2^; (7) have severe anemia (Hb < 10 g/dL); (8) are complicated by malignancy; (9) have a hypersensitivity or allergy to metformin and/or luseogliflozin; (10) have an alcohol consumption > 20 g/day; (11) have a smoking habit, including smoking even one cigarette per day, within 12 months before enrollment; (12) are participating in other clinical research within 6 months before enrollment; (13) are complicated by chronic liver disease with ≥ 6 points on the Child-Pugh score; (14) have a body mass index (BMI) < 18.5 kg/m^2^; and (15) are otherwise deemed inappropriate by the study’s principal investigator.

### Withdrawal criteria

Participants will be withdrawn from this trial after randomization if they meet any of the following criteria: (1) are exhibiting an increase in HbA1c level that is ≥ 0.5% of the baseline (week 0) for any two successive visits; (2) have a HbA1c level > 10.0% at any visit; (3) the occurrence of any AE that is ≥ grade 3 of the Common Terminology Criteria for Adverse Events (CTCAE) ver. 4.0; (4) are showing any fracture(s) with the exception of an occult fracture; (5) have requested withdrawal from the study; (6) have requested a change in, or the discontinuation of, the diabetes treatment; (7) it is determined that it is inappropriate for the patient to continue in the study by the investigators because of the progression of an underlying disease or a complication, or the occurrence of an unidentified disease; and (8) it is judged by the investigators that it is inappropriate for the patient to continue participating in the study for any other reason.

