### Outcomes

The primary outcome measures are changes in the predicted bone strength as determined by second-generation HR-pQCT, evaluated using the parameters of: (1) bone stiffness and (2) the estimated failure load of the radius and tibia of the nondominant body side. For each parameter, any change will be determined based on the difference between the measurement results at baseline (week 0) and week 48.

The study’s secondary outcome measures are as follows: (1) the changes in the structures of cortical bone, trabecular bone, and the bone morphology measured by HR-pQCT as described below in the “Image measurements” section from baseline (week 0) to week 48; (2) the changes in the laboratory data values, including the levels of glycated hemoglobin (HbA1c) from week 0 to weeks 12, 24, 36, and 48; (3) the changes in the areal BMD of the lumbar spine (L1–L4), femoral neck, and distal radius estimated by DXA from week 0 to week 48; (4) the incidence of vertebral fracture or femoral fracture from week 0 to week 48; and (5) changes in the bone metabolic markers from week 0 to week 48.

In addition to the primary and secondary outcomes, we will evaluate adverse effects from both luseogliflozin and metformin (control agent). We will also evaluate the recruitment rate and consent rate.

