### Statistical analyses

As stated above in the “Objectives” section, the primary outcome of this study is the extent of luseogliflozin’s effects on bone-quality change. Hence, the primary data analysis will be conducted using the set of participants with sufficient exposure to the allocated drugs. For this reason, we will use a per-protocol set (PPS), the definition of which includes the adherence ratio, as the target population in the primary data analysis. The same analyses will be conducted on a full analysis set (FAS) modified FAS (mFAS) to provide supplemental information about the influence of selecting PPS subjects on the results.

As the primary and the secondary data analyses, the adjusted mean and the 95% confidence intervals (95%CIs) of the bone-deterioration effect of the treatment group will be estimated as regression coefficient and its standard error, for the respective primary and secondary outcome measures, under a linear regression model with the following two covariates: the baseline measurement of the respective measures and the stratification factor in the randomization (i.e., sex). This study is set up as a pilot study, but we will test the null hypotheses that “the mean of the bone-quality deterioration effect of the treatment group is 0” by determining whether the 95%CIs contain the null hypotheses.

The respective analysis sets are defined as follows. The intention-to-treat (ITT) population is defined as all participants registered for this trial; the safety analysis set (SAS) population is defined as the participants in the ITT population with at least one administration of luseogliflozin/metformin. The full analysis set (FAS) population is defined as the participants in the SAS for whom data about the predicted bone strength after the administration of luseogliflozin/metformin at one or more scheduled visits are available. The PPS is defined as the participants in the FAS with the primary outcome measure. Other criteria for the PPS will be determined before the database lock of this study. We defined the modified FAS (mFAS), the definition of which is a relaxed version of PPS by allowing missingness of the data of predicted bone strength at week 48 only if the data of the items at withdrawal from this study are obtained.

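### Fracture incidence is a secondary outcome, yet a fracture that triggers withdrawal before week 48 takes the participant out of the PPS, and the linear model stated for all secondary outcomes does not fit this one

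*Protocol article*

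**What the plan says.** Secondary outcome (4) in the Outcomes section is "the incidence of vertebral fracture or femoral fracture from week 0 to week 48". Criterion (4) in the Withdrawal criteria section applies to participants who "are showing any fracture(s) with the exception of an occult fracture".

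The Statistical analyses section names one principal set: "we will use a per-protocol set (PPS), the definition of which includes the adherence ratio, as the target population in the primary data analysis". It adds: "The PPS is defined as the participants in the FAS with the primary outcome measure". The Outcomes section fixes that measure as the "difference between the measurement results at baseline (week 0) and week 48". FAS members are treated participants for whom "data about the predicted bone strength after the administration of luseogliflozin/metformin at one or more scheduled visits are available". The mFAS is a looser form of the PPS that accepts "missingness of the data of predicted bone strength at week 48 only if the data of the items at withdrawal from this study are obtained". The FAS and mFAS runs are described as supplementary, to show what selecting PPS subjects does to the results. Adverse-event incidence is tabulated on the SAS, which needs only one dose of study drug.

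The same section sets the analysis method "for the respective primary and secondary outcome measures, under a linear regression model with the following two covariates": the baseline value of the measure concerned, and sex. Fracture incidence is not excepted.

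Setting and study timeline requires an HR-pQCT scan within 4 weeks of stopping study drug for every withdrawal. Table 1 marks HR-pQCT in its withdrawal column but no x-ray.

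**The concern.** The outcome event can remove its own case from the set that carries the principal results. Concern about fracture with this drug class is what motivates the trial (Background and Discussion). A reader who finds no fractures in the principal set may take this as reassurance, when the only case was excluded because it fractured. The efficacy tables and the safety tables of one report could then give different fracture counts with no stated reason.

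The second problem is the model. The article does not leave the method for this outcome open. It assigns one, and that method needs a baseline value that an event counted from week 0 does not have.

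**Working it through.** **Inputs.** 24 participants allocated 1:1 (Study design) and 12 per group (Sample size estimation): 2 × 12 = 24, which reproduces the stated total. The article gives no power, effect size or expected fracture rate, so there is no further figure to reproduce.

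**1. Where does a participant go who is withdrawn for a non-occult fracture before week 48?**

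| Set | Member? | Reason |
|---|---|---|
| ITT, SAS | Yes | Registered; at least one dose taken |
| FAS | Undetermined | Yes if the withdrawal HR-pQCT counts as a scheduled visit, otherwise no; the term is not defined |
| mFAS | Conditional | Only if the withdrawal scan is obtained and any other PPS criteria are met |
| PPS | No | No week-48 value of the primary measure |

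A vertebral fracture first found on the week-48 x-ray is different. That x-ray belongs to the same visit as the week-48 HR-pQCT, so the finding need not remove anyone from the PPS.

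**2. Effect on a PPS count.** Suppose one of 12 participants in an arm fractures and is withdrawn, and everyone else completes.

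- All treated: 1/12 = 8.3%. Clopper-Pearson lower limit 1 − 0.975^(1/12) = 0.2%. The upper limit solves (1 − p)^12 + 12p(1 − p)^11 = 0.025, giving p = 38.5%.
- PPS: 0/11 = 0%.
- For comparison, a true 0/12 has an exact 95% upper limit of 1 − 0.025^(1/12) = 26.5%.

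The intervals show how little 12 per arm can say on any analysis set. The defect itself is the step from 1/12 to 0/11.

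**3. How likely is at least one fracture?** This is an illustration on assumed rates. The Background cites fracture adverse events of 4.0% and 2.6% in a trial of another drug, with its own follow-up. If those rates carried over, the expected number is 12 × 0.040 + 12 × 0.026 = 0.48 + 0.31 = 0.79, and P(at least one) = 1 − 0.96^12 × 0.974^12 = 0.55. With a common rate between 1% and 10%, 1 − (1 − p)^24 runs from 0.21 to 0.92. These rates are not specific to vertebral and femoral sites.

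**4. Does the stated model fit?** With intercept, treatment, sex and a baseline fracture value of 0 for everyone, the design matrix has 4 columns but rank 3, so the baseline coefficient cannot be estimated. Drop that column, and take 1/12 versus 0/12 with each arm half female and half male. Least squares then gives a difference of 0.083 (95% CI −0.090 to 0.257). The overall mean is 1/24, and the treatment and sex effects are each ±1/24. The fitted value for a control participant of the sex without the fracture is therefore 1/24 − 1/24 − 1/24 = −0.042, a negative probability.

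**5. Would a different test rescue an inference?** No. At 12 per arm, Fisher's exact test first falls below 0.05 at 5 versus 0 (p = 0.037); 4 versus 0 gives p = 0.093. Counts with exact intervals are the realistic summary.

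**The case against.** A reader might infer that a fracture removes the participant from the FAS as well. The article does not establish this. The FAS asks for post-dose bone-strength data, not week-48 data, and a scan is required at every withdrawal. The mFAS is built to admit such scans, and a modified FAS containing people outside the FAS would be odd. On the other side, Visit 6 is the only numbered post-dose visit with HR-pQCT, and the timeline section lists withdrawal apart from visits 1 to 6. The point is open, and that is all that can be said.

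A reader might also infer that fractures would disappear from the report. They would not: all adverse events are recorded and tabulated on the SAS, so a clinical fracture that triggers withdrawal should appear there. But that table is not designated as the analysis of secondary outcome (4).

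The PPS is tied in words to the primary data analysis, and no sentence expressly assigns it to fracture incidence. This stands, and it limits the claim: the article names no other principal set, and the FAS and mFAS are supplementary.

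Methods for single outcomes are often left to the analysis plan. That would excuse silence, but here the article states a method covering all secondary outcomes.

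Finally, one might call the missing x-ray at withdrawal an error. The text and Table 1 agree on it, so it is a design choice. It does mean that silent vertebral fractures in withdrawn participants are not sought.

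**Conclusion.** The point holds in this limited form. A non-occult fracture leading to withdrawal before week 48 places the participant outside the PPS. A PPS count of this outcome is then biased toward zero (1/12 becomes 0/11) and may contradict the SAS adverse-event table. FAS membership is undetermined and mFAS membership conditional. The linear model with a baseline covariate is assigned to this outcome and does not fit it.

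The conclusion on the PPS rests on the article's definitions alone. The 1/12 example assumes one such event and no other loss. The probabilities of any event rest on borrowed rates and are illustrative only.

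Severity is minor to moderate. Fracture is one of five secondary outcomes in a pilot of 24, the primary outcome is predicted bone strength, and recorded fractures still reach the safety tables. Calling it a defect that must be mended before the trial can proceed would go beyond what the documents support.

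**What to change.** Add one paragraph to Statistical analyses:

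- Exempt fracture incidence from the linear regression.
- Analyse it on the SAS, counting every vertebral or femoral fracture from first dose to week 48, including one that triggers withdrawal.
- Report counts by arm with Clopper-Pearson 95% intervals and no between-arm inference.
- Say whether the withdrawal HR-pQCT counts as a scheduled visit for the FAS.
- State as a limitation that no spinal x-ray is scheduled at withdrawal, so silent vertebral fractures in withdrawn participants are not ascertained.

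Outcomes, Withdrawal criteria, Setting and study timeline (with Table 1) and Statistical analyses should be reconciled on this point. No change to the withdrawal rule is proposed and none is needed. The cost is a short amendment or analysis-plan entry. It uses data already collected as adverse events and on the planned x-rays, and adds no procedure.

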### Ethical considerations

This protocol was approved by Clinical Research Review Board of Nagasaki University which is certified by Japan’s Ministry of Health, Labor, and Welfare (approval no. CRB18–0006). The study is registered on the University Hospital Medical Information Network Clinical Trials Registry (UMIN-CTR) as UMIN-CTR no. 000036202. The study is conducted in accordance with the 7th revision of the Declaration of Helsinki 2013 and the Clinical Trials Act enforced in April 2018 in Japan.

### Setting and study timeline

All participants are recruited at Nagasaki University Hospital. Each participant’s information as listed below is collected at the pre-screening for enrollment (visit 1); age, sex, height, comorbid complications, diabetes duration, history of diabetes treatment, family history of diabetes and osteoporosis within the second degree of kinship, and histories of smoking, drinking, and fracture. Body weight, blood pressure, and pulse rate in a sedentary position are measured at every visit of the study (at visits 1–6, and (if withdrawing from the study) at withdrawal). As shown in Table 1, the participants will undergo examinations by spinal x-ray, DXA, and HR-pQCT at week 0 (visit 2) and week 48 (visit 6). When participants need to be withdrawn from the study for any reason, they will undergo HR-pQCT within 4 weeks after discontinuing the study drug. Blood specimens are obtained at every visit except the pre-screening visit (visit 1).

**Table 1 Tab1:** The schedule of pre-screening, interventions, and assessments

Assessment	Pre-screening	Baseline	Monitoring				Withdrawal
Time	Day 60~ −1	Week 0	Week 12	Week 24	Week 36	Week 48	
Visit	Visit 1	Visit 2	Visit 3	Visit 4	Visit 5	Visit 6	
Informed consent	○	–	–	–	–	–	–
Baseline characterization check	○	–	–	–	–	–	–
Adherence check	–	–	•	•	•	•	•
Concomitant treatments							
Adverse events	–						
Vital signs	○	○	•	•	•	•	•
Laboratory data	–	○	•	•	•	•	•
X-ray	–	○	–	–	–	•	–
DXA (BMD measurement)	–	○	–	–	–	•	–
HR-pQCT	–	○	–	–	–	•	•

○ Will be done before initiating the study drug. Will be done after initiating the study drug

A range of ± 4 weeks is allowed for each visit day

The examination at withdrawal would be carried out within 4 weeks from the date of withdrawal

*BMD* bone mineral density, *DXA* dual-energy x-ray absorptiometry, *HR-pQCT* high-resolution, peripheral quantitative computed tomography

### Image measurements

Frontal and lateral x-ray examinations are performed to detect compression fractures of the thoracic and lumbar vertebrae using a semiquantitative technique [23]. DXA is performed for the assessment of the areal BMD at the lumbar spine (L1, L2, L3, L4, L1–4, L-min), total hip (right total, left total), femoral neck (right neck, left neck), and the distal third of the radius (right radius, left radius) using the DXA system (iDXA, GE Medical Systems, WI, USA). The second-generation HR-pQCT (Xtreme CT II, Scanco Medical, Brüttisellen, Switzerland) scans the radius and tibia of the nondominant body side to evaluate the bone microstructure.

We measure the following parameters by HR-pQCT: (1) bone density, i.e., total volumetric bone mineral density, trabecular volumetric bone mineral density, and cortical volumetric bone mineral density; (2) trabecular bone parameters, i.e., bone volume fraction, trabecular thickness, trabecular number, and trabecular separation; (3) cortical bone parameters, i.e., cortical thickness, cortical porosity, and cortical pore diameter; (4) bone morphology, i.e., total area, trabecular area, cortical area, and periosteal perimeter, and (5) predicted bone strength, i.e., stiffness and failure load.

### Laboratory measurements

At visits 3–5, we measure the patients’ complete blood count and plasma levels of sodium, potassium, chlorine, calcium, phosphate, magnesium, total protein, albumin, total cholesterol, high-density lipoprotein cholesterol, low-density lipoprotein cholesterol, triglyceride, blood urea nitrogen, creatinine, total bilirubin, aspartate aminotransferase, alanine aminotransferase, lactate dehydrogenase, alkaline phosphatase, γ-glutamyl transpeptidase, creatine kinase, uric acid, glucose, and HbA1c. At visit 2 and visit 6 (and at withdrawal if discontinuing participation), in addition to the above laboratory data, we measure the serum (plasma) levels of glycoalbumin, C-peptide, glucagon, glutamic acid decarboxylase antibody, intact PTH, whole PTH, free thyroxine, thyroid-stimulating hormone, adrenocorticotropic hormone, luteinizing hormone, follicle-stimulating hormone, total estradiol, total testosterone, sex hormone-binding globulin, total cortisol, growth hormone, insulin-like growth factor-1, homocysteine, glucagon, tartrate-resistant acid phosphatase 5b, total type I procollagen *N*-terminal propeptide, bone-specific alkaline phosphatase, undercarboxylated osteocalcin, osteocalcin, 25-hydroxyvitamin D, 1,25-dihydroxyviamin D, sclerostin, dickkopf-1, and pentosidine. There are no plans for the collection, laboratory evaluation, and storage of biological specimens for genetic or molecular analysis in the current trial and for future use in ancillary studies.

### Randomization and allocation concealment

A randomized, open-label, parallel pilot trial design has been set up. On the day on which the first administration of the study drug (visit 2) is planned after the eligibility assessment, each participant is sequentially allocated to either the luseogliflozin group or the control group in a 1:1 ratio, using a blocked randomization stratified by sex (female or male). The allocation is conducted by the participant-registration center, and the result is sent to the investigators via facsimile so that the block size and randomization schedule are concealed to the investigators, participants, and those assessing outcomes. As the study design is open-label with only outcome assessors being blinded, unblinding will not occur during the study.

### Interventions

1. Luseogliflozin group: participants allocated to the luseogliflozin group will take orally administered luseogliflozin (Taisho Pharma Co., Tokyo, Japan) at 2.5 mg/day from the beginning of the trial (visit 2) in addition to their previous treatment. The dose of luseogliflozin will be increased to 5 mg from visit 3 unless a participant achieves a HbA1c level < 7% or a decrease in the HbA1c of ≥ 0.5% compared to the previous visit. The maximum dose of luseogliflozin permitted is up to 5 mg/day. If a participant cannot achieve the HbA1c levels described above with 5 mg luseogliflozin, an additional treatment with metformin (Sumitomo Dainippon Pharma Co., Osaka, Japan) will be prescribed at each visit by 500-mg increments up to 1500 mg. The daily dose of metformin will be increased by 250 mg at each visit if the participant already takes ≥ 1500 mg/day. The maximum dose of metformin permitted is 2250 mg/day.

2. Control group (metformin group): participants allocated to the control group will have orally administered metformin 500 mg/day newly administered or added from the beginning of the trial (visit 2) in addition to the previous treatment. The additional metformin will be administered at each visit by 500-mg increments unless the participant achieves a HbA1c level < 7% or a decrease in HbA1c ≥ 0.5% compared to the previous visit. The daily dose of metformin will be increased by a 250-mg increment at each visit if the participant already takes ≥ 1500 mg/day. The maximum dose of metformin permitted is 2250 mg/day.

